### Patients

Delivery of pregnant women in Spanish maternity wards with a diagnostic test for COVID-19.

### Inclusion criteria:

- Single or multiple gestations of 24 weeks or more without a positive laboratory test for COVID-19 prior to delivery.
- Delivery in a public or private maternity hospital in Spain with a diagnostic test for COVID-19 using PCR Kits within 72 hours prior to delivery or 24 hours after delivery.
- The presence of comorbidity is not an exclusion criterion (asthma, diabetes mellitus, hypertension-preeclampsia, endocrine disorder, dermatological pathology or other obstetric or medical-surgical pathologies).
- Acceptance by the pregnant woman to participate in the study by means of informed consent for group study.

The result of the PCR test on a sample of nasopharyngeal and/or oropharyngeal swab was considered synonymous with exposure/non-exposure, defining a case as any pregnant woman with a positive result, regardless of the symptoms. Those cases with clinical presentation of COVID-19 were classified according to the WHO division for adults into: mild symptoms, mild-moderate pneumonia, severe pneumonia and septic shock (16).

The recommended samples for diagnosis are samples from the upper respiratory tract: nasopharyngeal and/or oropharyngeal swab.

A healthy patient is considered to have a negative PCR in the absence of symptoms. Patients with positive IgM or IgG serology cannot be included. The absence of serology does not prevent classifying the patient as healthy if the PCR is negative.

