### Design

Longitudinal cohort case study to quantify the obstetrical and perinatal morbi-mortality throughout all hospitals in Spain with a universal, consecutive PCR based screening program.

Recruitment: 1st March 2020 to 1st March 2021. Spanish sites collected in Appendix 1.

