## Substudy 4. Epidemiological prevalence study

### Objective/s

Determine the prevalence of SARS\_COV2 infection in Spanish pregnant women

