### Design

Cross-sectional study.

The nQuery Advisor Release 7.0 software was used to calculate the sample size, based on the available data. As we do not have data on the prevalence of COVID-19, we set an expected percentage of 50% (a situation that maximizes the sample size) of asymptomatic women during delivery. We determined the sample size for a COVID-19 delivery prevalence study with an expected prevalence of 50%, a 95% confidence level and 5% accuracy, resulting in a sample size of 1056 pregnant women.

The selection of pregnant women in the sample will follow the distribution of the delivery rate by communities and hospitals in Spain according to the INE data for 2018 (Appendix 3) (15). Subsequently, a simple random selection procedure will be carried out in each site, creating a numerical list of the women to be included in the sample (Appendix 1). Pregnant women will be assigned a consecutive number from one onwards according to their due date. Subsequently, the pregnant women who will be part of the sample will be chosen when the number that identifies them is within the table previously created through the random procedure.

Recruitment: 1st March 2020 to 1st March 2021. Spanish sites collected in the Appendix 1

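### Substudy 4 bars women with a positive test before delivery, yet its own PCR window opens 72 hours before delivery; read literally, cases detected in those hours are excluded and prevalence is biased downward

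*Protocol*

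**What the plan says.** All references are to the protocol.

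- **Substudy 4, Objective/s:** the single objective is the prevalence of infection "in Spanish pregnant women". It is not limited to newly detected infection.
- **Substudy 4, Inclusion criteria, first bullet:** "Single or multiple gestations of 24 weeks or more without a positive laboratory test for COVID-19 prior to delivery". There is no lower time limit and no exception for the study test.
- **Substudy 4, Inclusion criteria, second bullet:** delivery in a Spanish maternity hospital with a "diagnostic test for COVID-19 using PCR Kits within 72 hours prior to delivery or 24 hours after delivery".
- **Same section, case definition:** "defining a case as any pregnant woman with a positive result, regardless of the symptoms".
- **Same section, closing paragraph:** after defining a healthy patient as PCR-negative and symptom-free, it adds "Patients with positive IgM or IgG serology cannot be included". The same paragraph appears in the general Definitions section.
- **Substudy 4, Design:** women are drawn by simple random selection within sites, in proportion to national births, "with an expected prevalence of 50%, a 95% confidence level and 5% accuracy, resulting in a sample size of 1056 pregnant women".

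**The concern.** The two criteria apply jointly. A woman whose qualifying PCR is positive at, say, 24 hours before delivery satisfies the second and fails the first. A woman who tests negative at the same hour satisfies both. Eligibility therefore depends on the result that the substudy sets out to measure, and always in the same direction: positives leave and negatives remain. No other section resolves this.

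Since prevalence is the only objective, the headline estimate would be too low by an amount that cannot be read off the data collected. The random, nationally proportional selection would not protect it, because the loss occurs after selection. Sites could also apply the clause differently, some keeping women with a positive study PCR and some dropping them, so that pooled results would mix two populations.

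**Working it through.** **Plan's own figure.** The protocol gives no prevalence estimate to reproduce. Its only figure here is the sample size of 1056, used below solely to turn proportions into counts. Its stated inputs (50%, 95% confidence, ±5%) give 1.96² × 0.5 × 0.5 / 0.05² = 384.1, so 385, not 1056. That mismatch is a separate matter and has no bearing on this point.

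**Inputs.**
- Window: 72 h before to 24 h after delivery, 96 h in all (second inclusion bullet).
- N = 1056 women selected (Substudy 4, Design).
- p, the true PCR prevalence in the window: unknown to the protocol, so assumed at 1%, 3%, 5% and 10%.
- f, the share of in-window positives obtained before delivery: not given, possible range 0 to 1. It equals the share of all tests done before delivery if test timing is unrelated to infection. If tests were spread evenly over the window, f = 72/96 = 0.75.

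**Reading A: the clause covers any positive before delivery, including the study PCR.**
1. True cases among those selected: N·p.
2. Cases excluded: N·p·f. Cases kept: N·p·(1−f).
3. Women kept: N − N·p·f = N(1−fp).
4. Observed prevalence: p(1−f)/(1−fp).

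At p = 3%:
- f = 0.25: 0.0225/0.9925 = 2.27%
- f = 0.50: 0.0150/0.9850 = 1.52%
- f = 0.75: 0.0075/0.9775 = 0.77%

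| Assumed p | True cases in 1056 | f = 0.25: kept, observed | f = 0.50: kept, observed | f = 0.75: kept, observed |
|---|---|---|---|---|
| 1% | 10.6 | 7.9, 0.75% | 5.3, 0.50% | 2.6, 0.25% |
| 3% | 31.7 | 23.8, 2.27% | 15.8, 1.52% | 7.9, 0.77% |
| 5% | 52.8 | 39.6, 3.80% | 26.4, 2.56% | 13.2, 1.30% |
| 10% | 105.6 | 79.2, 7.69% | 52.8, 5.26% | 26.4, 2.70% |

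At f = 0 there is no bias; at f = 1 no case can enter. The fraction of in-window cases lost is exactly f.

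**Reading B: the clause covers only positives before the screening window opens.** Cases first detected in the window are kept, so the loss in the table disappears. Women diagnosed earlier in pregnancy and still PCR-positive at delivery are still excluded, although they are infected on the protocol's own case definition and belong to the population in the objective. The quantity estimated is then newly detected infection among women with no earlier positive test. The protocol gives no figure from which to size the difference.

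**The case against.** The best defence is that Reading A cannot have been intended. It would make the pre-delivery part of the window useless for finding cases and admit only women first found positive in the 24 hours after delivery. The same section expressly accepts earlier tests, counts any positive PCR as a case and grades cases by severity. Reading B is the more natural intention, and it gives a definable population. It would therefore be wrong to say that the estimate describes no defined population at all. What stands is that the text does not say so, and that Reading B is still narrower than the objective.

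Three stronger inferences are tempting and not supported.

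- **That most cases are lost.** This needs Reading A and f above 50%. The even-spread value of 75% is an assumption: hours of window are not a share of tests. The general selection criteria and Substudy 3 describe control screening at delivery or less than 3 days before, which makes a high f plausible but does not establish it for Substudy 4.
- **That the serology sentence removes PCR-positive women, or inflates prevalence by dropping seropositive negatives.** The sentence sits inside the definition of a healthy patient, and in context limits who is so classified. Placed under the inclusion criteria it invites misreading, but no effect can be sized: serology may be missing, and Safety Measures and Confidentiality says no extra tests are done.
- **That Substudy 4 must be confined to hospitals with universal screening.** Substudy 3 is set "throughout all hospitals in Spain with a universal, consecutive PCR based screening program"; Substudy 4 is not, and it admits only tested women. Where testing is selective, that is a real limitation. But restricting sites would cut into the national sampling, which Appendix 3 allocates across every listed province. It would be a trade-off, not a correction.

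**Conclusion.** The concern holds in this form: the first two inclusion criteria of Substudy 4 contradict each other as written and must be reconciled. Followed literally, they exclude every case detected in the 72 hours before delivery and bias prevalence downward whenever any positive is found before delivery. For an assumed true prevalence of 3%, the observed value would be about 2.3%, 1.5% or 0.8% for f of 25%, 50% or 75%. Both p and f are assumptions, and f could lie anywhere from 0 to 1.

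On the more lenient reading that bias vanishes, but women already diagnosed and still PCR-positive at delivery are left out of an estimate whose objective includes them. The need for a change therefore does not depend on f or on which reading was meant. The size of the loss does, and it should not be stated as fact.

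**What to change.** 1. Remove the prior-positive clause from the first inclusion criterion. At the least, state that the qualifying in-window PCR is exempt from it.
2. Count as a prevalent case every sampled woman with a positive PCR from 72 hours before to 24 hours after delivery.
3. Add a variable marking women with a positive test before the window, so that newly detected infection can be reported separately beside total prevalence.
4. If the sponsor wants only newly detected infection, keep an exclusion limited to positives before the window and restate the Substudy 4 objective to match.
5. State that the serology sentence governs only who is classified as healthy and is not an eligibility rule for the prevalence sample.
6. Report how many randomly selected women had no test in the window, so that readers can judge selection by testing. Restriction to universal-screening sites is not required.

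The cost is a wording amendment, one flag variable and one extra count in the report. No additional testing is needed. Women already set aside under the literal rule should be traceable, since the registry itself takes PCR-positive pregnant women, but they would have to be matched back to the random selection lists.

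### Substudy 4 bars women with positive serology, so entry to a random-sample prevalence study depends on which sites happen to test antibodies

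*Protocol*

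**What the plan says.** Substudy 4 has one objective: "Determine the prevalence of SARS\_COV2 infection in Spanish pregnant women". Its Design section calls it a "Cross-sectional study" in which "a simple random selection procedure will be carried out in each site, creating a numerical list of the women to be included in the sample". The number of women was worked out "with an expected prevalence of 50%, a 95% confidence level and 5% accuracy, resulting in a sample size of 1056 pregnant women".

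The section *Inclusion criteria* opens with four bullets:
- gestation of at least 24 weeks, with no positive laboratory test before delivery;
- a PCR between 72 hours before and 24 hours after delivery;
- comorbidity is no bar;
- consent.

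No bullet sets a condition on symptoms or names antibodies. Under the same heading, the text then treats the PCR result as equivalent to exposure status, "defining a case as any pregnant woman with a positive result, regardless of the symptoms". Three sentences follow at the end:
- One describes who counts as healthy: "A healthy patient is considered to have a negative PCR in the absence of symptoms".
- The next sets the serology bar: "Patients with positive IgM or IgG serology cannot be included".
- The last deals with women who had no antibody test: "The absence of serology does not prevent classifying the patient as healthy if the PCR is negative".

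The same three sentences stand in the registry-wide section *Definition of case and healthy patient for the study*. The section *Safety Measures and Confidentiality* says that laboratory tests are those each site performs under its own protocol, with none added for the study.

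**The concern.** A cross-sectional prevalence from a random sample needs every selected, eligible woman with a valid result to be counted, whatever else is known about her. A serology bar breaks this, because antibody status is related to infection status. It also acts unevenly, because it can apply only to women who happened to be tested. Sites with routine serology lose women whom other sites would keep, which undoes part of the proportional allocation in Appendix 3.

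The scope of the sentence is open. Its place under the inclusion criteria suggests that it bars any seropositive woman, including PCR-positive ones. Its place after the description of a healthy patient suggests that it restricts only the PCR-negative group. The two readings push the estimate in opposite directions. Because this is an entry rule, women left out cannot be restored at the analysis.

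**Working it through.** **The plan's own figure.** With p = 0.5 and half-width d = 0.05, n = 1.96² × p(1 − p)/d² = 3.8415 × 0.25/0.0025 = 384.1, so 385 and not 1056. At 50%, 1056 women give a half-width of 1.96 × √(0.25/1056) = 3.02 points. That mismatch is a separate matter. Here 1056 serves only as the planned number of women.

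**Formula.** Let p be the true PCR prevalence among otherwise eligible women. Let s1 and s0 be the shares of PCR-positive and PCR-negative women removed by the bar. Each share is the fraction who had serology times the fraction positive among them. Then

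observed prevalence = p(1 − s1) / [p(1 − s1) + (1 − p)(1 − s0)].

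The true odds are multiplied by (1 − s1)/(1 − s0). The estimate is too high if s1 < s0 and too low if s1 > s0. The protocol gives none of p, s1 or s0, so every value below is an assumption.

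**Reading A: the bar restricts only PCR-negative women (s1 = 0).**

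| True p | s0 = 5% | s0 = 10% | s0 = 20% |
|---|---|---|---|
| 2% | 2.10% | 2.22% | 2.49% |
| 5% | 5.25% | 5.52% | 6.17% |

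For example, 0.05/(0.05 + 0.95 × 0.80) = 0.05/0.81 = 6.17%.

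**Reading B: the bar applies to all women (true p = 5%).**

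| s1 | s0 | Working | Observed |
|---|---|---|---|
| 20% | 10% | 0.040/(0.040 + 0.855) | 4.47% |
| 50% | 5% | 0.025/(0.025 + 0.9025) | 2.70% |
| 80% | 2% | 0.010/(0.010 + 0.931) | 1.06% |

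**Dependence on site.** A site that does no serology has s1 = s0 = 0 and reports the true 5%. Under reading A, a site where the bar removes 10% of PCR-negative women reports 5.5% for the same population.

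**Against sampling error.** A simple binomial half-width at 5% with 1056 women is 1.96 × √(0.05 × 0.95/1056) = 1.31 points. The largest shift under reading A is 6.17 − 5 = 1.17 points, which is inside it. Under reading B the shifts run from 5 − 4.47 = 0.53 to 5 − 1.06 = 3.94 points, so they can exceed it.

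**The case against.** The strongest defence is that healthy is only a label. The four bullets contain no symptom or antibody condition. The disputed sentences come after them and repeat a registry-wide definition. The Statistics section of Substudy 4 compares women by infection status, so a healthy group has a use there. On this view the sample is simply every selected woman with a PCR.

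Part of this stands. A reader might infer that PCR-negative women with symptoms are dropped from the denominator while symptomatic PCR-positive women stay. The protocol does not say so. No sentence removes these women, and the same section makes PCR alone the classifier. What remains is an inconsistency: such a woman counts as non-exposed by PCR but is not healthy by definition. A reader might also infer that the plan states a wrong prevalence denominator. It states none, and the exact estimator may be in a statistical analysis plan that is not at hand.

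The defence does not rescue the serology sentence. It speaks of inclusion, it stands under the inclusion heading, and nothing confines it to a comparison group. Substudy 3, by contrast, accepts PCR-positive cases whatever another serological test shows.

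A second defence is that past infection was meant to be excluded, since the first bullet already bars women with an earlier positive test. That intent is plausible. But a bar that works only where serology was done does not define a target population.

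Third, under reading A the bias stays within sampling error in every scenario shown. That is true, but a larger sample would not reduce it, and reading B is not covered by that argument.

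**Conclusion.** The concern holds for the serology sentence. As written, it makes eligibility for a random-sample prevalence study depend on local antibody testing, and its scope is ambiguous enough that even the sign of the bias is unknown. If it acts on PCR-negatives only, a true 5% becomes 5.2-6.2% with 5-20% of them removed. If it acts on all women, 5% becomes about 1.1-4.5% with 20-80% of PCR-positives and 2-10% of PCR-negatives removed. The downward result requires seropositivity to be commoner among PCR-positives. All these shares are assumed, and the effect may be small if few women are tested or few are seropositive.

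The symptom condition is a lesser matter: it leaves symptomatic PCR-negative women unclassified but does not expressly exclude them.

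**What to change.** - Remove the three healthy-patient and serology sentences from the Substudy 4 inclusion criteria, or limit them expressly to comparison groups. All three must go together, because the one on missing serology has no meaning alone.
- State that the serology bar in the registry-wide definition does not govern eligibility for Substudy 4.
- Define the denominator as every selected woman who meets the four bulleted criteria and has a valid PCR in the window, whatever her symptoms or serology. Define the numerator as the PCR-positive women among them.
- Clarify that the earlier positive test in the first bullet means neither serology nor the in-window PCR. That PCR may be taken up to 72 hours before delivery, so read literally the bullet could bar the very cases being counted.
- Describe the result as prevalence among women without an earlier positive test.
- Report symptoms and available serology descriptively.

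The cost is a short change of wording. It needs no extra tests, data items or patients.

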### **Primary variables**

|                                      |                                |
|--------------------------------------|--------------------------------|
| Age                                  | Delivery < 37 weeks            |
| Race                                 | Delivery Type                  |
| Weight at the beginning of pregnancy | Premature rupture of membranes |
| Body Mass Index (BMI)                | Preterm PRM                    |
| Blood type                           | NICU admission                 |
| Single or Multiple                   | NICU admission days            |
| IVF                                  | Postpartum haemorrhage         |
| Obesity BMI> 30                      | Abruptio placentae             |
| Vascular comorbidities               | Severe Preeclampsia            |
| Pulmonary comorbidity                | HELLP                          |
| Maternal mortality                   | Pulmonary embolism             |
| ICU admission                        | COVID 19 diagnosis date        |

The rest of the variables are described in appendix 5

## Statistics

For the statistical analysis, the SAS v9.4 software will be used.

The set of groups of variables requested and collected for each enrolled patient will be the same. The demographic and clinical characteristics of the population included will be summarized. Mean, standard deviation, minimum and maximum or median and interquartile intervals will be used for continuous variables, according to the distribution. The corresponding absolute and relative frequency will be reported for the discrete variables.

The possible association of both the characteristics of the patients and the *outcomes* collected with COVID-19 infection using the Pearson Chi-square test or Fisher's exact test and the Mann-Whitney U test (after checking the absence of normal data using the Kolmogorov-Smirnov test). Statistically significant associations were considered when the p value was less than 0.05. For those categorical variables in which statistically significant differences were identified, the corresponding Odds Ratio (OR) and 95% Confidence Intervals (95% CI) were estimated using univariate logistic regression models.

Logistic regressions, both univariate and multivariate, will be performed, determining the odd ratio and its 95% confidence interval.

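### Substudy 4 is designed and sized to estimate prevalence, but its primary variables and analysis do not carry prevalence through and instead declare associations significant at an unadjusted 0.05

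*Protocol*

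**What the plan says.** The section titled "Substudy 4. Epidemiological prevalence study" states a single objective, which is to determine how common SARS-CoV-2 is: "infection in Spanish pregnant women". Its Design section sizes the sample by precision alone, "with an expected prevalence of 50%, a 95% confidence level and 5% accuracy, resulting in a sample size of 1056 pregnant women". It gives no power and no effect size for any comparison.

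The Primary variables table of Substudy 4 has 12 rows in two columns, so 24 entries. They are maternal characteristics, comorbidities, delivery and neonatal outcomes, and "COVID 19 diagnosis date". The PCR result and the prevalence are not among them. A note adds: "The rest of the variables are described in appendix 5".

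The Statistics section of Substudy 4 plans:
- descriptive summaries, including absolute and relative frequencies for discrete variables;
- chi-square, Fisher or Mann-Whitney tests of characteristics and outcomes against infection, with the rule "Statistically significant associations were considered when the p value was less than 0.05";
- odds ratios with 95% intervals from univariate logistic models for the categorical variables that pass that rule;
- univariate and multivariate logistic regressions in general.

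It names no interval for the prevalence, ranks no test, mentions no adjustment for multiplicity and does not call the tests exploratory.

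**The concern.** The objective and sizing point to one quantity, while the variables called primary and all the inference point elsewhere. A team following the last two sections literally would report a list of significant associations and need not report the prevalence with its uncertainty.

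Two consequences follow. First, readers cannot separate a planned finding from a chance one, because some two dozen tests carry the same label at the same threshold. Second, estimating odds ratios only where p is below 0.05 selects the larger estimates, so the reported set is biased away from the null. The closing sentence on logistic regression in general does not say whether this condition is lifted.

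Twelve of the outcomes are also compared between infected and uninfected women in Substudy 3 at the same threshold. Nothing says how a Substudy 4 result on them is to be read beside the Substudy 3 result.

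**Working it through.** **1. The plan's own figure.** The only quantitative target in Substudy 4 is the precision of prevalence. With n = z²p(1−p)/d², z = 1.96, p = 0.50 and d = 0.05:

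n = 3.8416 × 0.25 / 0.0025 = 384.2, so 385.

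The stated 1056 does not follow from these inputs. At 1056 the 95% half-width is 1.96 × √(0.25/1056) = 0.030 at 50% prevalence, and by the same formula 0.013 at 5% and 0.006 at 1%. The mismatch in sample size is a separate matter. What counts here is that the number was set for prevalence and for nothing else.

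**2. Objective to analysis, side by side.**

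| Part of Substudy 4 | Is prevalence there? |
|---|---|
| Objective | Yes, and it is the only one |
| Design (sample size) | Yes, it is the sizing basis |
| Primary variables | No; 24 other entries |
| Statistics | No interval; at most a relative frequency |

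**3. Number of tests.** 24 entries less the diagnosis date, which exists only in cases and cannot be compared by infection status, leaves 23. Variables in Appendix 5 and the regression models could add more; their number is not shown.

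**4. Chance of at least one false significant result**, all 23 null hypotheses true, each test at 0.05 two-sided (sidedness is assumed):
- expected number: 23 × 0.05 = 1.15;
- independent tests: 1 − 0.95²³ = 0.693;
- equal correlation ρ between normal test statistics: 1 − ∫ φ(t) · [Φ((c − √ρ·t)/√(1−ρ)) − Φ((−c − √ρ·t)/√(1−ρ))]²³ dt, with c = 1.96. This gives 0.449 at ρ = 0.5 and 0.235 at ρ = 0.8.

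The values of ρ are assumptions. Some correlation is certain: weight, BMI and obesity; premature and preterm rupture of membranes; NICU admission and NICU days.

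**5. Allowance for rare outcomes.** Exact tests on rare events reject less often than 5%. Event rates of 0.01% to 15% were assumed for 16 binary variables, the other 7 were left at a full 0.05, and independence was kept. The chance of at least one false result is then:

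| Assumed prevalence | Positives among 1056 | Chance of ≥1 false result |
|---|---|---|
| 1% | 11 | 46% |
| 3% | 32 | 52% |
| 5% | 53 | 52% |
| 10% | 106 | 56% |
| 50% | 528 | 63% |

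Correlation would lower these again. The event rates and prevalences are illustrative; the Protocol gives none except the planning value of 50%.

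**6. Overlap with Substudy 3.** Twelve outcomes stand in both lists: ICU admission, delivery before 37 weeks, delivery type, premature rupture of membranes, preterm rupture, NICU admission, NICU days, postpartum haemorrhage, abruptio placentae, severe preeclampsia, HELLP and pulmonary embolism.

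**The case against.** The strongest reply is that the target is not in doubt. The objective and Design sections name delivery prevalence, the inclusion criteria fix the case definition and testing window, and the relative frequency of PCR-positive women is the prevalence. Interval methods are often left to an analysis plan, which is not at hand. Across all four substudies, the primary variables heading introduces a list of main data items (age and diagnosis date appear there too), not endpoints. Much of this stands. A reader might infer that Substudy 4 has no identifiable main analysis; the documents do not support that. What remains is that the two sections governing reporting leave the target out while fixing a significance rule for other things.

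A reader might also infer that a false association is likely. That needs independent, full-size tests and every null true. With moderate correlation or rare outcomes the chance is near or below one half. Nor should these figures be expressed as multiples of 5%: the Protocol sets 0.05 per test and promises no family-wise rate.

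Finally, one might infer an open conflict with Substudy 3. The objectives already point the other way. Substudy 3 exists to compare obstetric morbidity and has adjusted models for it, and Substudy 4 has no morbidity objective. Its population also differs, since women with a positive test before delivery are excluded. The overlap needs a sentence, but it is not two equal attempts at one hypothesis.

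**Conclusion.** The point holds as a failure to carry the objective through. Prevalence is the sole objective and sizing basis, yet it is absent from the primary variables, and no confidence interval for it is planned. In its place the Statistics section labels associations significant at an unadjusted 0.05 and makes univariate odds ratios for categorical variables conditional on that label.

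If there are no true associations, the chance of at least one false significant result among 23 tests is roughly 24% to 69%, depending on correlation, and lower where rare outcomes make the tests conservative. These figures assume two-sided tests of the listed variables only; Appendix 5 variables and the regressions could raise them. No Substudy 4 association is designated confirmatory, so the harm is misleading reporting rather than an invalid study. It should be corrected because the correction is simple.

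**What to change.** In the Primary variables and Statistics sections of Substudy 4:
- name the proportion of women PCR-positive at delivery, with its 95% confidence interval, as the primary variable and primary analysis;
- label the listed variables, and their associations with infection, as descriptive or exploratory;
- report odds ratios with 95% confidence intervals for all of these associations for which an odds ratio is defined, whatever the p-value, and remove the condition that ties them to p below 0.05;
- state that, for the outcomes shared with Substudy 3, the Substudy 4 results are supportive only.

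The cost is a wording amendment to the Protocol or analysis plan, with no new data. The downside is that Substudy 4 can no longer headline individual associations as significant.
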